### Qualitative substudy

We will integrate qualitative research throughout the feasibility study, with the overall aim of identifying and understanding issues that might threaten the viability of a full-scale future RCT. This includes issues of recruitment and informed consent, and acceptability of the interventions and proposed outcome measure assessments.

The specific objectives of the integrated qualitative research are to:

investigate healthcare professionals’ perspectives on the trial design, including perceptions of equipoise, views on the eligibility criteria, relevance of the primary and secondary outcomes, and approaches to measuring these.understand the acceptability of randomisation from patients’ perspectives, with a focus on reasons for accepting/declining trial participation and factors that influenced these decisions.explore patients’ experiences of trial participation, including perceived acceptability of being in the intervention/control arms and undergoing outcome assessments (eg, CPET, wearing accelerometers).

We will address the above objectives by conducting semistructured interviews with healthcare professionals and patients who accept and decline trial participation. Both healthcare professionals and patients will be sampled across all six sites. We anticipate up to 40 interviews will be conducted (20 patients, 20 clinical professionals) over the 2-year study period.

### Progression to full-scale RCT

This feasibility study aims to test the processes of a proposed future multicentre RCT and therefore we will use a traffic-light approach to determine trial progression according to the following indices:

Patient participation:Green: > 40% of approached patients consent to trial participation.Amber: Between 30% and 40% of approached patients consent.Red: < 30% of patients consent.Adherence to randomisation and study completion:Green: > 85% of enrolled participants received the allocated intervention and completed both CPETs without withdrawing.Amber: Between 75% and 85% completion rate.Red: < 75% completion rate.

We anticipate that a green light for the above indices will realise patient recruitment and retention rates within a future full-scale RCT to enable scheduled completion. In response to an amber trigger, the Trial Management Group (TMG) will develop strategies that specifically respond to potential issues with patient participation that have been highlighted by the qualitative analysis. We would not proceed to a full-scale trial if a red signal is triggered.

During this feasibility study, we expect that, once open, each of the participating centres recruits a minimum of one patient per month and that fistula disconnection is performed within 62 days of CPET. If not met, the TMG will attempt to identify and address systematic problems that may hinder the main RCT.

### Sample size

As this is a feasibility study, formal sample size calculation is not required. We will therefore aim to recruit 40 patients (in keeping with recommendations^42^), 20 in each arm, with progression to a future RCT dependent on meeting set criteria relating to participant recruitment and retention rates as above. If the percentage of patients completing the study is 85%, 40 patients will give a 95% CI (70.2 to 94.3).

### Randomisation

Randomisation of consenting participants will be stratified according to fistula site (wrist or elbow) and fistula volume flow (low or high), as determined by a pre-randomisation Doppler ultrasound of the fistula, and allocated in a 1:1 ratio to the intervention (surgical disconnection of fistula) or to standard care (continued conservative management) using an interactive web response system provided by Sealed Envelope. Fistula flow rate will be measured during baseline assessment visits and categorised as either low flow (wrist AVF: ≤800 mL/min, elbow AVF: ≤1400 mL/min) or high flow (wrist AVF: >800 mL/min, elbow AVF: >1400 mL/min). The research team will confirm to the clinical and surgical teams which arm of the trial the participant has been randomised to, with the intervention being performed by a vascular access/transplant surgeon within 62 days of completion of baseline assessments. Given the surgical nature of the intervention, there will be no blinding in this trial with all participants, clinical and research team members aware of which trial arm is assigned at randomisation.

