## Objectives

To conduct a feasibility study involving six centres, that mirrors a proposed full-scale RCT, with predefined cut-offs with regards patient recruitment and retention rates to justify progression to the larger RCT.To understand patients’ and healthcare professionals’ perceived acceptability of the proposed trial design and processes.To assess feasibility and acceptability of CPET in the kidney transplant population, as judged by the proportion of participants who successfully complete both tests.To assess patient compliance with wearing a wrist-worn accelerometer (physical activity measurement).

Our longer term objective is to use the findings regarding recruitment and retention from this feasibility study to inform the design and powering of a future multicentre RCT that will test the hypothesis:

In stable renal transplant patients, fistula disconnection improves cardiorespiratory fitness, thereby increasing patients’ activity levels and improving QoL.

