### Outcomes

For this feasibility study, the primary outcome measure will be the proportion of approached patients who complete the study, defined as the proportion of eligible approached patients that consent, receive the allocated intervention, and complete both CPET tests without withdrawing.

Secondary outcomes are subdivided into: those related to the feasibility of the study; clinical measures that will be measured at baseline and 6 months following intervention, and the differences in these values; and safety outcome measures occurring between study consent and the 6-month assessment visit.

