#### Clinical outcome measures

Peak VO_2_ as measured during incremental CPET on a cycle ergometer.Physical functioning domain score of Short Form-36 Quality of Life questionnaire.^38^Activity levels (mean daily Euclidean norm minus one) as calculated from accelerometry data collected from provided wrist-worn accelerometer device over 7-day period at baseline and following 6-month assessment.Serum N-terminal pro B-type natriuretic peptide value.Office blood pressure.Additional CPET indices: ventilatory anaerobic threshold, endurance time, peak workload, O_2_ pulse, VO_2_/work rate slope (VO_2_/WR), minute ventilation/CO_2_ output slope (VE/VCO_2_), heart rate/VO_2_ slope (HR/VO_2_), perceived exertion rating (Borg scale).Additional domain scores of the Short Form-36 QoL questionnaire^38^: physical role limitation, emotional role limitation, energy/ fatigue, emotional well-being, social functioning, pain, general health, perceived health change.Kidney transplant function (eGFR by CKD-EPI estimation^37^).Fistula-related symptoms reported in modified Vascular Access Specific QoL questionnaire^39^ (for all participants at enrolment, and at 6 months for cohort randomised to standard care).Proportion of participants with at least one major adverse cardiovascular event (MACE)^40^: cardiovascular death; ischaemic cardiovascular event (myocardial infarction, percutaneous coronary intervention, coronary artery bypass graft); hospitalisation for heart failure at any time during the 6-month study period.

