### Statistical methods

The analysis of the primary outcome of the proportion of approached patients who complete the study successfully will include the proportion of eligible approached patients who consented, received the allocated intervention, completed both CPET tests and did not withdraw, with 95% CIs. As part of the intention-to-treat approach, those who have graft failure, die, or are lost to follow-up will be included in the analysis of the primary outcome as not completing the study successfully. The component proportions and the corresponding 95% CIs of the primary outcome will be presented as secondary outcomes.

The secondary feasibility outcomes of recruitment rate by trial site and the proportion of participants who were compliant with wearing wrist accelerometers, and their 95% CIs, will also be presented. Compliance to wearing the monitor will be assessed by measuring wear time. The days from providing consent to first CPET and the days from CPET to fistula disconnection will be summarised, and the median and IQR presented. Patient and healthcare professional perceived acceptability of the trial design and processes will be analysed using qualitative analysis.

Descriptive statistics of the secondary clinical outcomes will be presented for each arm separately, at baseline, the 6-month assessment, and the average change over time, with 95% CIs. Peak VO_2_ will also be presented by fistula site and according to prespecified flow rate categories. Very limited hypothesis testing will be conducted but mixed linear regression will be used to examine any difference in peak VO_2_ at 6 months between the two treatment arms, with adjustment for fistula site, flow rate, baseline peak VO_2_ and centre. Fistula-related symptoms will be assessed using the modified VASQoL questionnaire for all participants at enrolment and at 6 months for the standard care arm and compared where applicable. The proportion of participants who experienced at least one MACE by 6 months will be presented (alongside 95% CIs), and details of all reported MACEs listed. In addition, summaries of all secondary safety outcomes will be presented by arm.

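### The surgical nature of the intervention justifies unblinding participants and treating teams, but not the reading of the 6-month CPET traces or, where staff are separate, the running of the test

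*Protocol article*

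**What the plan says.** The Randomisation section is explicit: "there will be no blinding in this trial with all participants, clinical and research team members aware of which trial arm" each person is in. The only reason it gives is that the intervention is surgical. No other section of the article qualifies this. None provides for a CPET operator who is unaware of allocation or for trace reading without arm labels, and the strengths and limitations list does not mention the matter.

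On the outcomes, the article says the following:

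- **Primary outcome (Outcomes):** "the primary outcome measure will be the proportion of approached patients who complete the study", a feasibility proportion.
- **Clinical outcomes (Clinical outcome measures):** the first listed is peak VO2, "as measured during incremental CPET on a cycle ergometer". Further down come "Additional CPET indices: ventilatory anaerobic threshold, endurance time, peak workload" and others, including a Borg rating of perceived exertion.
- **Analysis (Statistical methods):** "Very limited hypothesis testing will be conducted but mixed linear regression will be used to examine any difference in peak"; the quantity compared is the 6-month peak VO2 of the two arms, adjusted for fistula site, flow rate, baseline value and centre. No other outcome has a named between-arm model.
- **Purpose (Objectives):** the study "mirrors a proposed full-scale RCT", and the RCT's hypothesis is that disconnection improves cardiorespiratory fitness.

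**The concern.** The article gives one reason for having no blinding, and that reason reaches only some of the people it is applied to. A participant knows whether the fistula has been ligated, and so does the surgeon. The person who reads a 6-month gas-exchange trace has no need to know. The person who supervises the test may have no need to know either, if that person is not part of the treating or research team.

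This matters because an incremental test taken to peak, together with endurance time, peak workload and the Borg rating, can respond to encouragement and to the decision to stop. The ventilatory anaerobic threshold also requires a judgement by the reader. The article does not call these measures effort-dependent or reader-dependent; that is inferred from what they are.

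Two things are at stake. One is how the peak VO2 comparison in this study is interpreted. The other is whether the study tests an assessment procedure fit for the RCT, whose hypothesis concerns the same quantity.

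**Working it through.** **1. Who the stated reason covers**

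| Role | Does surgery force knowledge of the arm? |
|---|---|
| Participant | Yes |
| Surgeon and treating team | Yes |
| CPET operator at 6 months | Not in itself; depends on whether the operator is also treating or research staff, and on visible signs |
| Reader of CPET traces | No |

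The Randomisation section treats all participants, clinical staff and research staff alike.

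**2. Which test is exposed**

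The abstract places CPET at recruitment and 6 months later, so the second test takes place after allocation is known. Adjustment for baseline peak VO2 in the model cannot remove a bias that arises only at follow-up.

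**3. What depends on the value of peak VO2**

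- Primary outcome: consent, receipt of allocation and completion of both tests without withdrawal. The value is not used.
- Progression criteria: the consent rate (green above 40%) and the completion rate (green above 85%). The value is not used.
- Mixed linear regression at 6 months: the value is the dependent variable.
- RCT hypothesis: it concerns cardiorespiratory fitness, for which the Introduction names peak VO2 as the principal CPET index.

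**4. The plan's own figure**

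The only precision figure is in Sample size: 85% completion of 40 patients, 95% CI 70.2 to 94.3. With 0.85 × 40 = 34 completers, the exact Clopper-Pearson interval for 34/40 is 70.2% to 94.3%, which reproduces it. The point made here does not rest on this figure, but it supplies 34/2 = 17 completers per arm for the next step.

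**5. Illustration of size**

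The document gives no SD for peak VO2 and no bias size. Assume no true effect, a normal approximation, two-sided alpha of 0.05, and an assessor-induced shift of b residual SDs in favour of ligation. Then

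SE of the difference = SD × √(2/n per arm), and

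P(reject) = 1 − Φ(1.96 − b/SE) + Φ(−1.96 − b/SE).

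SE is √(2/20) = 0.316 SD with 20 per arm and √(2/17) = 0.343 SD with 17.

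| Assumed shift b (SD) | 20 per arm | 17 per arm |
|---|---|---|
| 0 | 5.0% | 5.0% |
| 0.1 | 6.2% | 6.0% |
| 0.2 | 9.7% | 9.0% |
| 0.3 | 15.8% | 14.1% |
| 0.5 | 35.3% | 30.8% |

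The 95% CI half-width is 1.96 × 0.316 = 0.62 SD with 20 per arm and 1.96 × 0.343 = 0.67 SD with 17. A shift of 0.1 to 0.2 SD is therefore well inside the noise of this study.

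A bias of fixed size matters more as n grows. With an assumed 150 per arm, SE = √(2/150) = 0.115 SD. The same shifts are then 0.87 and 1.73 SE, and the rejection rates are about 14% and 41%. The article gives no RCT sample size, so these two figures rest on two assumptions and describe a trial not yet designed.

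**The case against.** There are good arguments on the other side.

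- **Little hangs on peak VO2 here.** It is secondary, tested within a deliberately minimal set of hypothesis tests, and absent from the progression rules. This stands. A reader might infer that the feasibility result or the go/no-go decision is biased; the Outcomes and Progression sections do not support that.
- **Most of the effort comes from an unblinded participant.** This stands too. Masking the operator does not stop participants from trying harder or less hard according to their arm. Scars or a patent fistula can also reveal the arm, and so can the modified VASQoL, which is given at 6 months to the standard care arm only. It would be wrong to conclude that masking would remove the bias.
- **The larger error rates are hypothetical.** This stands. The 14% and 41% figures need an assumed bias and an assumed RCT size, and should not be read as properties of this trial. The RCT is still to be designed, so masking could be specified there.
- **Staffing is not described.** The article does not say who runs or reads the CPET. If research staff do, masking the operator might need other people. This limits what can be asked about operators. Reading files without arm labels needs only existing staff.
- **A condensed article may omit a CPET manual.** Agreed: silence about standardised encouragement or stopping criteria is no evidence that coaching is uncontrolled. The blinding statement is different, because it is a positive decision with a stated reason.
- **Open-label assessment is common in small feasibility studies.** It is, and this one is openly declared. That does not make the stated reason cover trace reading, and whether CPET staff can stay unaware of the arm is a process that a study mirroring the RCT is well placed to test.

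**Conclusion.** The point holds in a limited form. The surgical nature of the intervention does not justify reading the 6-month CPET traces with the arm known or, where operators are separate staff, running the test with the arm known. The exposure is confined to the modelled peak VO2 comparison, reader-judged indices such as the ventilatory anaerobic threshold, and the assessment process carried into the RCT. The primary outcome and the progression decision are essentially unaffected, and no change to the sample size follows.

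The size of the bias cannot be determined from the document. Under an assumed 0.1 to 0.2 SD shift, the effect on this trial's one named test is small: about 6 to 9% instead of 5% with 17 per arm. The effort-dependence of the measures is an inference, and only the part of the bias that comes from readers and separate operators is avoidable. The change is worth making because it is cheap and tests a process the RCT will need.

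**What to change.** In the Randomisation section, limit the open-label statement to participants and the treating and surgical teams. Then add:

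1. Existing staff read the CPET files with arm labels removed.
2. CPET operators who are not part of the treating or research team are not told the allocation, and the 6-month VASQoL is completed away from the CPET.
3. The CRF records whether the operator was aware of the arm, and this is reported as a feasibility measure.
4. Where a site cannot do this, the report states it as a limitation.

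The cost is a site instruction and one CRF item, with no extra visits or procedures. Under item 2, no new personnel are required: where research staff run the test, item 4 applies. The downside is that masking will sometimes fail; item 3 shows how often, which is useful for designing the RCT.

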### Statistical methods

The analysis of the primary outcome of the proportion of approached patients who complete the study successfully will include the proportion of eligible approached patients who consented, received the allocated intervention, completed both CPET tests and did not withdraw, with 95% CIs. As part of the intention-to-treat approach, those who have graft failure, die, or are lost to follow-up will be included in the analysis of the primary outcome as not completing the study successfully. The component proportions and the corresponding 95% CIs of the primary outcome will be presented as secondary outcomes.

The secondary feasibility outcomes of recruitment rate by trial site and the proportion of participants who were compliant with wearing wrist accelerometers, and their 95% CIs, will also be presented. Compliance to wearing the monitor will be assessed by measuring wear time. The days from providing consent to first CPET and the days from CPET to fistula disconnection will be summarised, and the median and IQR presented. Patient and healthcare professional perceived acceptability of the trial design and processes will be analysed using qualitative analysis.

Descriptive statistics of the secondary clinical outcomes will be presented for each arm separately, at baseline, the 6-month assessment, and the average change over time, with 95% CIs. Peak VO_2_ will also be presented by fistula site and according to prespecified flow rate categories. Very limited hypothesis testing will be conducted but mixed linear regression will be used to examine any difference in peak VO_2_ at 6 months between the two treatment arms, with adjustment for fistula site, flow rate, baseline peak VO_2_ and centre. Fistula-related symptoms will be assessed using the modified VASQoL questionnaire for all participants at enrolment and at 6 months for the standard care arm and compared where applicable. The proportion of participants who experienced at least one MACE by 6 months will be presented (alongside 95% CIs), and details of all reported MACEs listed. In addition, summaries of all secondary safety outcomes will be presented by arm.

## Patient and public involvement

The views of both kidney transplant patients and members of the public were sought during the design of this study, both through Patient and Public Advisory Group (PPAG) meetings and distributed surveys, with final oversight from local kidney patient groups. Key aspects of the study protocol were developed following these discussions with both adaptation to the study inclusion criteria and greater emphasis placed on the incorporation of QoL assessment and daily functioning.

The feasibility study has been designed such that continued patient involvement will be a core aspect, with the integrated qualitative research aimed at capturing the participant experience and generating insight into the factors that may undermine recruitment and threaten the viability of a full-scale RCT.

We have included a patient representative as part of the TMG and will also conduct 6 monthly PPI meetings during the feasibility study, with lay-person involvement, to moderate discussions with patient and clinicians on their views of trial participation.

We have already established close links with local kidney patient groups at each of the trial centres; the qualitative analysis will be shared with these groups; and we anticipate that the ensuing discussions with both patients and public will promote awareness of the study, facilitate patient recruitment and retention as well as support the dissemination of results and design of the subsequent RCT.

## Ethics and dissemination

This study has been approved by the East Midlands—Derby Research Ethics Committee (22/EM/0002) and the Health Research Authority. Research will be conducted in compliance with the approved protocol, the Declaration of Helsinki (2013), the Principles of Good Clinical Practice, the UK Data Protection Act, the UK Framework for Health and Social Care Research and any other applicable national regulations. Written informed consent will be obtained from the participants by a suitably qualified member of the clinical/research team who has received trial training. The patient’s right to refuse participation in the trial and withdraw from the study at any time and without reason will be respected, without prejudice to their further treatment.

The results of this trial will be presented to academic and non-academic groups with PPAG involvement in disseminating the study findings into the public domain. Open access, peer-reviewed academic outputs and research reports together with associated summaries and key findings will be produced and held on the study website.

## Access to data

Access to the final dataset will be available on request from [name], [contact], after the trial results have been published (expected September 2024) and should continue to be available for 4 years. No identifiable data will be shared. All participants have provided their written informed consent for their data to be used in this way.

